#### Key secondary endpoints (man analytical approach)

Occurrence of MAKE_90_ and its components will be analysed using a Cochran-Mantel–Haenszel model to estimate of the common relative risk (pooled RMC-035 versus placebo) across the stratification group formed by eGFR at Day −1 (≥ 60 and < 60 mL/min/1.73m^2^). The estimate of the common relative risk, 90% CI utilizing Greenland and Robins, and *p*-value will be reported. The proportion of participants with MAKE_90_ and each MAKE_90_ component, and its 90% CI will be calculated.

Change from baseline in eGFR at Day 90 (by each RMC-035 dose level) will be analysed using the same model as the primary endpoint, but where treatment will include both dose levels of RMC-035 and difference versus placebo will be estimated for each dose level.

Occurrence of MAKE_90_ and its components by each RMC-035 dose level will be analysed using the same model as for the pooled treatment group analyses, but where treatment will include both dose levels of RMC-035 and relative risk versus placebo will be estimated for each dose level.

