**Inclusion criteria**
Participants are eligible to be included in the study only if all of the following criteria apply:
1. Age is ≥ 18 and < 85 years at the time of signing the informed consent
2. eGFR is ≥ 30 ml/min/1.73m^2^ (at screening) using the CKD-EPI 2021 equation with SCr [9]
3. Scheduled for non-emergent surgery of any or several of the following types with use of CPB:
a. CABG surgery
b. Valve surgery (single or multiple valves)
c. Ascending aorta aneurysm surgery
4. Risk factors for kidney injury are present (at screening) as specified below:
a. eGFR is < 60 mL/min/1.73m^2^ with or without additional risk factors from list (1) to (8) below present, regardless of whether single type or combined surgery is planned
b. If eGFR is ≥ 60 mL/min/1.73m^2^
i. A combined surgery is scheduled AND at least one risk factor for kidney injury from list (1) to (8) below is present
ii. One type of surgery is scheduled AND at least two risk factors for kidney injury from list (1) to (8) below are present
Risk factors for AKI:
(1) Documented history of LVEF < 35% at any time during the 3-month period before or at the time of screening as assessed by either echocardiography, cardiac MRI or nuclear scan
(2) Repeat surgery/history of previous open chest cavity cardiac surgery with or without CPB
(3) Confirmed diagnosis of T2DM at least 3 months prior to screening AND ongoing treatment with an approved anti-diabetic drug
(4) Age ≥ 70 years at the time of screening
(5) Documented history of NYHA class II or higher at any time during the
(6) 3-month period before or at the time of screening
(7) Documented history of AKI as per KDIGO criteria longer than 3 months before date of screening, independent of the etiology of AKI
(8) Documented history of anaemia with haemoglobin ≤ 11 g/dL at any time during the 3-month period before or at the time of screening
(9) Documented history of albuminuria, defined as UACR > 100 mg/g in a spot urine sample or > 100 mg/24 h in a 24-h urine collection at any time during the 3-month period before or at the time of screening
5. Female Participants:
• A female participant is eligible to participate if she is not pregnant or breastfeeding, and one of the following conditions applies:
a. Is a WONCBP
b. Is a WOCB) and using a contraceptive method that is highly effective (with a failure rate of < 1% per year), with low user dependency, during the study intervention period and for at least 7 days after the last dose of study intervention

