### Outcomes {12}

All endpoints involving eGFR are based on the CKD Epidemiology Collaboration (CKD-EPI) equation of 2021 using SCr assessed in a central laboratory [9]. Calculations of eGFR based on CKD-EPI equations using centrally sampled CysC [12] and a combination of SCr and CysC [9] are used for sensitivity analyses.

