### Participant timeline {13}

The study consists of 8 visits for each participant, and has three study periods:Visit 1: Screening period of 30 days (Day −30 to Day −1)◦ Day −1, the day before surgery, is a required study timepoint for randomisation and sampling of first baseline SCrVisits 2 to 6: Treatment and hospital stay period of approximately 7 days (Day 1 to Day 7)◦ Day 1 before the patient is prepared for surgery is the required timepoint for sampling of second baseline SCr◦ Treatment with study drug occurs on Day 1 at 0 and 6 h, and Day 2 at 24 h◦ Hospital stay continues until discharge at approximately Day 7Visits 7 and 8: Follow-up period until Day 90 (from discharge to Day 90)◦ First follow up visit at 60 days after surgery◦ Second and last follow up visit at 90 days after surgery

During the course of the study, visits and assessments will be performed as visualised in the study flow chart [Fig. 1] and as defined in the schedule of assessments for the full study period [Table 3] and for Days 1 and 2 [Table 4].

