## Assignment of interventions: allocation

### Sequence generation {16a}

Participants are randomised block wise in a 2:2:3 ratio to RMC-035 high dose, RMC low dose, and placebo, respectively. Stratification for eGFR (≥ 60 and < 60 mL/min/1.73m^2^) will be implemented, and at least 30% of participants will be included in the < 60 mL/min/1.73m^2^ stratum.

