### Concealment mechanism {16b}

Stratified randomisation to IMP is done centrally using an interactive response technology (IRT) based upon patient information entered by the study site staff: age, gender and SCr. Blinded study site staff does not become aware of the intervention assignment.

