### Methods for additional analyses (e.g. subgroup analyses) {20b}

Subgroup analyses of the primary endpoint and secondary endpoints will be performed to assess consistency of the investigational intervention effect across the following subgroups:eGFR at Screening < 60 mL/min/1.73m^2^ versus ≥ 60 mL/min/1.73 m.^2^Diabetes mellitus at Screening: Yes and NoRegion: North America and EuropeGender: Male and Female

If the number of participants is too small (less than 10%) within a subgroup, then the subgroup categories may be redefined prior to unblinding the study. The analyses will be conducted using a test for heterogeneity and results will be presented on forest plots presenting the estimated study arm difference and 90% confidence intervals.

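### The eGFR <60/≥60 factor is dated differently in the MAKE90 analysis and the subgroup analysis, the creatinine that sets the randomised stratum is not identified, and the primary MMRM leaves the factor out

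*Protocol article*

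**What the plan says.** The same cut-off appears in several places in the protocol article:

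- **Sequence generation {16a}:** "Stratification for eGFR (≥ 60 and < 60 mL/min/1.73m^2^) will be implemented". No sampling day or laboratory is given. The same sentence reserves at least 30% of participants for the lower stratum.
- **Concealment mechanism {16b}:** the IRT randomises "based upon patient information entered by the study site staff: age, gender and SCr". Which creatinine sample is meant is not stated.
- **Key secondary endpoints, analytical approach:** the Cochran-Mantel-Haenszel (CMH) relative risk for MAKE90 is pooled "across the stratification group formed by eGFR at Day −1".
- **Methods for additional analyses {20b}:** the first subgroup is "eGFR at Screening < 60 mL/min/1.73m^2^ versus" 60 or above.
- **Participant timeline {13}:** "Screening period of 30 days (Day −30 to Day −1"; Day −1 is also the day of randomisation and of the first baseline creatinine.
- **Table 4:** local and central creatinine are both listed under Visit 1.
- **Primary endpoint (main analytical approach):** the MMRM has group, time and their interaction as fixed factors, with participant as a random factor. There is no eGFR stratum term.

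**The concern.** A factor used to stratify randomisation is normally carried into the analysis as it was randomised. Here the article names a time point twice and the two differ, while the randomisation sections name none. A participant screened two or three weeks before surgery can have a screening creatinine and a separate Day −1 creatinine, and near 60 these can point to different groups.

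This subgroup matters more than the others. Sample size {14} takes its effect assumption from the below-60 subgroup of the preceding trial, and the 30% floor protects that stratum here. If the stratified MAKE90 analysis and the eGFR subgroup analysis rest on different classifications, their results for one factor describe partly different people. An analyst would also be free to choose between samples. Separately, leaving the stratum out of the MMRM gives up whatever precision it would bring.

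**Working it through.** **The plan's own figures.** The article gives no reclassification rate to reproduce. Its relevant numbers are 46 + 46 + 69 = 161 participants and a floor of 0.30 × 161 ≈ 48 in the lower stratum. The sample size (difference 5, SD 12, two-sided 10%, 80% power, allocation 92:69) comes out at 63 + 84 = 147 evaluable, and 147/0.90 ≈ 163, close to 161. It involves no stratum term, so this point does not touch it.

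**Could the samples differ?** Day −1 lies inside the screening window, so for a participant screened on Day −1 the two labels can coincide. For anyone with an earlier screening creatinine they need not.

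**How many could change group?** Assumed inputs:

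- True eGFR is normal with SD s_b of 15, 18 or 20, and 30% truly below 60 (borrowed from the floor), so the mean is 60 + 0.524 × s_b.
- Two readings carry independent errors with SD s_e of 3, 5 or 7.
- The middle s_e is suggested by Sample size {14}, which attributes a fall in the SD of change from about 13 to 12 to duplicate sampling. Error variance in a change score is 2s_e² with single samples and s_e² with duplicates, so s_e² ≈ 13² − 12² = 25 and s_e ≈ 5. Both SDs are rounded, so this is only a guide.

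Formulas: v = s_b² + s_e²; ρ = s_b²/v; p = Φ((60 − mean)/√v); disagreement = 2 × [p − P(both readings below 60)].

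Middle case (s_b = 18, s_e = 5): mean 69.4; v = 324 + 25 = 349; ρ = 0.928; p = 0.307; both below 60 = 0.253; disagreement 10.7%, or 17 of 161. Among those below 60 on one reading, about 17% are at or above 60 on the other.

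| s_b | s_e = 3 | s_e = 5 | s_e = 7 |
|---|---|---|---|
| 15 | 7.8% | 12.7% | 17.2% |
| 18 | 6.5% | 10.7% | 14.6% |
| 20 | 5.8% | 9.6% | 13.2% |

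The range is about 6% to 17%, or 9 to 28 of 161. A variant with proportional errors (CV 4% to 10%; baseline mean/SD 60/15, 65/18 or 70/20) gives 5% to 18%.

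**Does the MAKE90 result change?** Simulation of 6,000 trials of 161 per scenario, with randomisation blocked within strata set by one reading and analysis by that reading or a second one. Assumptions: baseline mean 65, SD 18; 8% CV per reading; placebo MAKE90 risk 25% below 60 and 15% otherwise.

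| True RR | Strata used | Mean log RR | Rejection at two-sided 10% |
|---|---|---|---|
| 1.0 | randomised | 0.005 | 8.9% |
| 1.0 | re-measured | 0.005 | 8.9% |
| 0.6 | randomised | −0.522 | 36.9% |
| 0.6 | re-measured | −0.522 | 37.0% |

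**MMRM.** Adding the stratum changes the residual variance at Day 90 from σ² to about σ²(1 − R²), where R² is the share of variation in eGFR change that it explains. The article gives no R², so the gain cannot be sized. It is zero if the stratum does not predict change.

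**The case against.** The strongest reply is that these are loose labels for one grouping. Randomisation takes place on Day −1, the MAKE90 paragraph calls its groups the stratification group, and Table 4 places randomisation and the creatinine tests in the single screening column. On that reading the CMH strata already are the randomised strata, and the screening subgroup may be too. This stands as a possibility, and it is why the point is one of inconsistent labelling and not of demonstrated mismatch. It does not close the gap for participants whose screening sample predates Day −1.

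Several stronger readings are tempting but unsupported:

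- **Three competing definitions.** The randomised stratum is under-specified; nothing shows that it differs from the Day −1 group.
- **A local-versus-central mismatch between randomisation and the MAKE90 analysis.** No section says the site-entered creatinine is local, and the rule "All endpoints involving eGFR are based on the CKD Epidemiology Collaboration (CKD-EPI) equation of 2021 using SCr assessed in a central laboratory" covers endpoints, not a stratification factor. Same-day local and central values would also share the patient's state that day, so the 6% to 17% would overstate their disagreement.
- **A separate grouping behind the 30% floor.** The floor is stated for the randomised stratum itself.
- **An invalid or unbalanced analysis.** Every candidate value is pre-treatment, and the simulation shows no material change.

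It is also fair that MAKE90 is declared unpowered, that the subgroups are consistency checks, and that the separate analysis plan, not shown, may settle the sample and add the stratum to the model. The article nevertheless states two different time points itself, which goes beyond leaving a detail open.

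**Conclusion.** The point holds as an inconsistency in labelling, together with omission of the stratification factor from the primary model as described. The article does not ensure that the MAKE90 strata, the eGFR subgroup and the randomised strata are the same groups. If the samples differ and their errors are independent, roughly 6% to 17% of participants could be classified differently, given the assumed SDs and 30% truly below 60.

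The consequence is modest. No test is invalidated, the MAKE90 estimate and its error rate hardly move, and the sample size is unaffected. What can be gained is an eGFR subgroup that corresponds to the randomised strata, one analyst choice closed before unblinding, and a somewhat tighter primary estimate if the stratum predicts eGFR change.

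**What to change.** State which creatinine sample (day and laboratory) sets the IRT stratum. Then use the stratum recorded in the IRT at randomisation in three places: the CMH analysis of MAKE90, the MMRM as a fixed factor, and the eGFR subgroup analysis. Add, as a sensitivity analysis, the subgroup defined by central-laboratory baseline eGFR (mean of Day −1 and Day 1).

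The cost is wording in the analysis plan, to be settled before unblinding; the stratum is already recorded and no new data are needed. The one drawback is that participants mis-stratified on the site-entered value stay in that stratum, which the sensitivity analysis covers.

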### Sample size {14}

A total of 161 participants will be randomised in a 2:2:3 ratio across three study arms: 46 for RMC-035 low dose, 46 for RMC-035 high dose, and 69 for placebo.

This design aims to achieve at least 80% power to detect a significant effect of pooled dose levels compared to placebo at a 10% two-sided significance level, assuming a treatment effect of 5 mL/min/1.73m^2^ and a standard deviation of 12 mL/min/1.73m^2^. The expected effect size is conservatively based on observations from the AKITA study in the subgroup with eGFR < 60 mL/min/1.73m^2^, where a lower starting dose was administered [8]. In this subgroup, descriptive analysis indicated a difference in eGFR of 6.5 mL/min/1.73m^2^, while a mixed model of repeated measures (MMRM) showed 7.9 mL/min/1.73m^2^. The standard deviation was derived from the AKITA study, which reported approximately 13 mL/min/1.73m^2^. To minimise variability, double assessment of centrally sampled serum creatinine at baseline, days 60 and 90 will be used for eGFR calculation, with an expected standard deviation of 12 mL/min/1.73m^2^ in the current study. A 10% drop-out rate is anticipated for the 90-day assessment, along with a 5% information loss.

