Notably, the primary endpoint, eGFR change from baseline, and key secondary endpoints such as MAKE, are assessed at Day 90. This approach enables the evaluation of renal function in a stable phase after surgery, minimizing the influence of peri- and postoperative confounders. Furthermore, this approach is favored by regulatory authorities and represents a paradigm shift in “AKI trials”, which traditionally assess interventions based on short-term endpoints, such as AKI defined by KDIGO [17] or the recommendation to use AKI as primary endpoint in prevention trials [18], supported by observational trial data linking AKI occurrence and/or postoperative SCr increase with adverse long-term renal outcomes [3, 10, 18]. However, emerging data has increasingly highlighted the limitations of short-term endpoints:The degree of renal impairment, presence or absence of cellular injury, and potential for irreversible loss of kidney function cannot be sufficiently discriminated due to the absence of appropriate diagnostic tools, such as kidney biopsies or robust biomarkers [2].Tissue injury predisposing to permanent renal function loss may be obscured by postoperative improvements in cardiac output and renal blood flow, as well as the activation of functional renal reserve. This can mask nephron loss through hyperfiltration within the remaining nephrons [3].Minor and transient increases in SCr, reaching AKI stage 1 or remaining below this threshold – most commonly observed after surgery and often attributed to hemodynamic changes – are likely unmodifiable.Event rates for clinically meaningful short-term renal outcomes, such as RRT and/or severe AKI, even in high-risk patient groups, are typically below 10%. A robust assessment of these outcomes before a large pivotal phase 3 study is therefore infeasible.

These points are also reinforced by recent data from both interventional and observational AKI trials, demonstrating that many cardiac surgery patients who do not meet formal AKI criteria still experience irreversible and clinically significant eGFR loss, and vice versa [19, 20].

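### The Greenland-Robins interval prescribed for each MAKE90 component is undefined when an arm has no events, so death and RRT need a comparison measure that survives zero counts

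*Protocol article*

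**What the plan says.** The protocol article, in the Key secondary endpoints part of Statistical methods {20a}, analyses MAKE90 and its components by a Cochran-Mantel-Haenszel approach. It estimates a common relative risk of pooled RMC-035 against placebo over two strata, eGFR at Day −1 below 60 and at or above 60. The result is to be reported with a "90% CI utilizing Greenland and Robins" and a p-value. The method then carries over to the single doses: "Occurrence of MAKE_90_ and its components by each RMC-035 dose level will be analysed using the same model" used for the pooled comparison. The same section also reports, for MAKE90 and each component, the proportion with its own 90% CI.

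Under Objectives {7}, the components are death, new RRT, and an eGFR decline of 25% or more. Sample size {14} gives the arms as "46 for RMC-035 low dose, 46 for RMC-035 high dose, and 69 for placebo".

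On event rates, the Discussion says that clinically meaningful short-term renal outcomes "such as RRT and/or severe AKI, even in high-risk patient groups, are typically below 10" per cent. It also cites up to 30% for a sustained eGFR decline and describes MAKE90 as having a low event rate. No separate rate is given for death or for RRT. Full statistical detail is left to a SAP that is not shown.

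**The concern.** The Greenland-Robins variance of the log relative risk has a product of two event sums, one per arm, in its denominator. If one arm has no events over both strata, its sum is zero. The relative risk is then 0 or infinite, and no interval can be formed. The plan names this method for every component and every dose, so it also applies to death and RRT in arms of 46 against 69.

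What is at stake is the interval for the treatment comparison. The trial is meant to inform dose choice and benefit-risk for phase 3. If a dose arm has no deaths and placebo has two, a reader will want to know what size of difference is compatible with the data, and the prescribed interval cannot say.

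**Working it through.** **Inputs.** Arm sizes come from Sample size {14}. They agree with the 2:2:3 ratio: 161/7 = 23, so 2 × 23 = 46 per dose and 3 × 23 = 69 on placebo, with 92 pooled. The total was set for the eGFR endpoint and implies nothing about component event rates. The risks p below are therefore assumptions. The strata sizes in step 1 (16 and 30 on a dose, 23 and 46 on placebo) are illustrative.

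**Step 1: when the interval fails.** In each stratum let a of n1 on active and b of n0 on placebo have the event, with N = n1 + n0. Then

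- R = Σ a·n0/N, S = Σ b·n1/N, RR = R/S
- var(log RR) = Σ[(n1·n0·(a+b) − a·b·N)/N²] / (R·S)

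*No events on active:* 0/16 vs 1/23 and 0/30 vs 1/46.
- R = 0 and S = 16/39 + 30/76 = 0.805, so RR = 0.
- The variance numerator is 368/1521 + 1380/5776 = 0.481. The denominator is 0 × 0.805 = 0, so there is no interval.

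*No events on placebo:* S = 0, RR is infinite, and there is no interval. *No events in either arm:* everything is 0/0.

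*Zero in one stratum only:* 1/16 vs 2/23 and 0/30 vs 1/46.
- R = 23/39 = 0.590, S = 32/39 + 30/76 = 1.215, RR = 0.49.
- The variance is (1026/1521 + 1380/5776)/(0.590 × 1.215) = 1.27, and the 90% CI is 0.08 to 3.11.
- So a zero in a single stratum does no harm. The failure needs an arm that is empty across both strata.

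**Step 2: how often an arm is empty.** P(no events among n) = (1 − p)^n. With equal true risk p:

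- one dose vs placebo: 1 − [1 − (1−p)^46]·[1 − (1−p)^69]
- at least one of the two dose comparisons: 1 − [1 − (1−p)^46]²·[1 − (1−p)^69]
- pooled vs placebo: 1 − [1 − (1−p)^92]·[1 − (1−p)^69]

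At p = 2%: 0.98^46 = 0.395, 0.98^69 = 0.248, 0.98^92 = 0.156. One dose: 1 − 0.605 × 0.752 = 0.545. Pooled: 1 − 0.844 × 0.752 = 0.365.

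| Assumed risk of the component | One dose vs placebo | At least one of two doses | Pooled vs placebo |
|---|---|---|---|
| 1% | 81.5% | 93.1% | 69.8% |
| 2% | 54.5% | 72.5% | 36.5% |
| 3% | 33.8% | 50.1% | 17.6% |
| 5% | 12.1% | 20.4% | 3.8% |
| 10% | 0.9% | 1.6% | 0.1% |

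The interval is more likely missing than not below a risk of about 2.2% (one dose), 3.0% (at least one of two doses) or 1.5% (pooled). If the active risk is half the placebo risk, one dose comparison fails with probability 72%, 56%, 33% or 10% at a placebo risk of 2%, 3%, 5% or 10%. These figures use the full randomised arms; losses would only raise them.

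**Step 3: what survives.** The per-arm proportions and their intervals do not depend on the relative risk. With events only on placebo, RR = 0 is still an estimate and the CMH p-value can be computed. The p-value is lost only if both arms are empty: for one dose, (1−p)^(46+69), which is 0.98^115 ≈ 10% at 2% risk and 0.95^115 ≈ 0.3% at 5%.

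**Step 4: the eGFR component.** At the cited 30%, an empty dose arm has probability 0.70^46, below one in a million.

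**Step 5: the alternative in the failing example.** The Mantel-Haenszel risk difference is Σ[(a·n0 − b·n1)/N] / Σ[n1·n0/N] = −0.805/(368/39 + 1380/76) = −0.805/27.59 = −2.9 percentage points. It is finite, and a score-type interval can be put around it.

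**The case against.** The strongest objection is that the reporting of zero-event arms is a detail for the SAP. The SAP exists by reference and is not shown, and the relative risk is a legitimate measure. This stands in part: the absence of a zero-event rule from a condensed article is no fault. But the article names the estimator and the interval, and for sparse components that named method cannot deliver its own output.

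A reader might infer that the interval will probably be missing for death and RRT. The documents do not support that. They give no rate for death and none for RRT alone. Their only nearby figure, below 10%, concerns short-term RRT and/or severe AKI together, and at 10% the failure probability for one dose is about 1%.

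A reader might also infer that a difference in death or RRT could not be assessed at all. That is not supported either. Per-arm proportions with 90% intervals are prescribed, the safety section summarises fatal and serious events by arm, and the CMH p-value is lost only when both arms are empty. What these do not supply is an interval for the difference between arms.

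Finally, the Discussion says that MAKE90 is not powered and carries no multiplicity adjustment, and no stated decision rule uses the component relative risks. This limits the weight of the point and does not remove it.

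**Conclusion.** The point holds as a minor one. The prescribed interval is undefined whenever an arm has no events across both strata; that is algebra and needs no assumption. How often it happens rests on component risks that the documents do not give. Over an assumed equal risk of 1% to 10%, it ranges from 81.5% down to 0.9% for a single dose and from 69.8% down to 0.1% for the pooled doses. The issue is confined to death and RRT, and to the interval for the treatment comparison. The eGFR-decline component, and the composite that contains it, are essentially untouched at the cited rate.

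**What to change.** Keep the planned relative risk. For the death and RRT components, add the risk difference against placebo, stratified by Day −1 eGFR, with a score-type (Miettinen-Nurminen) 90% CI, for the pooled doses and for each dose. This stays computable with zero events in an arm and bounds the difference. An exact stratified p-value is optional.

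The cost is a sentence in the SAP and a column in the tables. The downside is a second effect measure beside the relative risk. It should be settled before unblinding. If the SAP already provides for this, the sponsor need only confirm it.
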